## Abstract

**Background:**

Stroke is a leading cause of mortality and disability, and its sequelae are associated with inadequate food intake which can lead to sarcopenia. The aim of this study is to verify the effectiveness of creatine supplementation on functional capacity, strength, and changes in muscle mass during hospitalization for stroke compared to usual care. An exploratory subanalysis will be performed to assess the inflammatory profiles of all participants, in addition to a follow-up 90 days after stroke, to verify functional capacity, muscle strength, mortality, and quality of life.

**Methods:**

Randomized, double-blind, unicenter, parallel-group trial including individuals with ischemic stroke in the acute phase. The duration of the trial for the individual subject will be approximately 90 days, and each subject will attend a maximum of three visits. Clinical, biochemical, anthropometric, body composition, muscle strength, functional capacity, degree of dependence, and quality of life assessments will be performed. Thirty participants will be divided into two groups: intervention (patients will intake one sachet containing 10g of creatine twice a day) and control (patients will intake one sachet containing 10g of placebo [maltodextrin] twice a day). Both groups will receive supplementation with powdered milk protein serum isolate to achieve the goal of 1.5g of protein/kg of body weight/day and daily physiotherapy according to the current rehabilitation guidelines for patients with stroke. Supplementation will be offered during the 7-day hospitalization. The primary outcomes will be functional capacity, strength, and changes in muscle mass after the intervention as assessed by the Modified Rankin Scale, Timed Up and Go test, handgrip strength, 30-s chair stand test, muscle ultrasonography, electrical bioimpedance, and identification of muscle degradation markers by D3-methylhistidine. Follow-up will be performed 90 days after stroke to verify functional capacity, muscle strength, mortality, and quality of life.

**Discussion:**

The older population has specific nutrient needs, especially for muscle mass and function maintenance. Considering that stroke is a potentially disabling event that can lead the affected individual to present with numerous sequelae, it is crucial to study the mechanisms of muscle mass loss and understand how adequate supplementation can help these patients to better recover.

**Trial registration:**

The Brazilian Clinical Trials Registry (ReBEC) RBR-9q7gg4. Registered on 21 January 2019.

## Background

Stroke is an important public health problem and is one of the leading causes of death in Brazil [1]. Stroke is the main cause of disability in the adult population, and approximately two-thirds of patients experience an incomplete recovery. Malnutrition on admission, reduced level of consciousness, dysphagia, and enteral tube feeding use may impair the nutritional status of these individuals, who generally become more susceptible to involuntary weight loss at this stage [2, 3].

Studies on the acute phase of stroke have shown that patients who were malnourished at the time of ictus had more complications and higher mortality rates than patients with adequate weight, overweight, or obesity [4].

After stroke, appetite loss, dysphagia, depression, changes in mobility, and functional dependence can lead to inadequate food intake, which is associated with neurological damage. Moreover, bed rest compromises nutritional status, resulting in a negative effect on physical and cognitive abilities [5, 6].

A previous study on patients in the acute phase of stroke demonstrated that individuals with some degree of dysphagia at the time of hospital discharge had higher mortality rates, regardless of stroke severity and other clinical factors, which may indicate the importance of adequate nutritional management during hospitalization for stroke and monitoring after hospital discharge for patients with food intake difficulties [7].

Malnutrition has been associated with inflammation and metabolic stress, which are proportional to injury severity, and increased protein catabolism, hypermetabolism, and insulin resistance [8].

Sarcopenia is associated with aging and is commonly observed in patients after stroke. Sarcopenia is considered primary when the patient has skeletal muscle mass decline, reduced water content, and increased body fat, or secondary to chronic or disabling diseases such as stroke [8, 9].

Unlike age-related sarcopenia, stroke-related sarcopenia has specific characteristics, such as rapid muscle mass decline and structural changes. The type of stroke and location and size of the brain injury are important factors affecting the differences in physical and functional performance, depending on the side affected by stroke, which is independent of age. Moreover, catabolic signals from brain damage can result in an imbalance in the neurovegetative state. Therefore, there is a complex metabolic and systemic change in individuals with stroke that can lead to weight loss and reduced anabolism, worsening the prognosis [10]. Muscle changes occur within 4 h after stroke, and over 7 days, patients can develop muscle weakness on both the affected and contralateral sides of the body [11].

Daily intake of 1.2 to 1.5 g of protein per kg of body weight is recommended along with exercise for sarcopenia prevention in older adults, as this population is more susceptible to inadequate protein intake for several aging-related reasons leading to increased proteolysis and anabolic resistance [12, 13]. However, limited data are available regarding the prevention of sarcopenia or malnutrition in the acute phase after stroke.

Some nutrients and amino acids such as creatine appear to be potential compounds capable of promoting hypertrophy and improving muscle function. Creatine supplementation has been proven effective in improving muscle mass in healthy older individuals, even when only taken for a few days; in pathological conditions, these positive results are supported by studies in several populations [14–17].

A combination of resistance exercise and adequate protein intake is recommended to maintain healthy skeletal muscles. However, there is no recommendation for this type of multimodal therapy in older people after stroke. Evidence is scarce regarding the influence of protein supplementation and specific amino acids associated with physical activity on the functional capacity and quality of life among this population.

The aim of the study is to verify the effectiveness of creatine supplementation on functional capacity, strength, and changes in muscle mass during hospitalization for stroke compared to usual care. A descriptive and comparative evaluation between groups in order to verify the inflammatory and potential serum biomarkers behavior during hospitalization will be performed with all participants randomized. A follow-up 90 days after stroke to verify functional capacity, muscle strength, mortality, and quality of life will be carried out.

## Methods

### Trial design

It will be a (randomization 1:1 to the intervention or control groups) double-blind (participants and researchers responsible for administering the supplement and carrying out the protocol assessments), unicenter, parallel-group trial including individuals with ischemic stroke in the acute phase to verify the superiority of the intervention compared to the control group. The duration of the trial for the individual subject will be approximately 90 days, and each subject will attend a maximum of three visits. The protocol was written according to the 2013 Standard Protocol Items: Recommendations for Interventional Trials (SPIRIT) guidelines. A flow diagram of the study is presented in Fig. 1.

**Fig. 1 Fig1:**
[figure not shown]
Flow diagram of the ICaRUS Stroke Trial

### Participants and eligibility criteria

Men and women aged 60 years and older who were diagnosed with ischemic stroke without previous disability (Modified Rankin Scale [mRs] – [mRs≤2]) and agree to sign the informed consent form will be recruited within 24 h of stroke.

Patients with any of the following will not be included: hemodynamic instability, mechanical ventilation, pacemakers and metallic prostheses, previous kidney disease, creatinine clearance ≤30 ml/min/1.73 m^2^, history of disabsorptive gastrointestinal surgery, parenteral nutrition, allergies or intolerance to any component of the study products, and patients who decline to participate.

The study will be conducted at the Stroke Unit of the Clinical Hospital of Botucatu Medical School, Brazil, and the follow-up visits at the Neurovascular Disease Outpatient Clinic of the same institution.

### Interventions

Creatine supplementation will be administered in the intervention group to avoid the muscle loss that is common in patients after stroke. The control group will receive maltodextrin, a complex carbohydrate with no direct effect on muscle loss. All participants will receive the same amount of protein per kg of body weight so that the groups are homogeneous in the consumption of this nutrient. The intervention will proceed as follows:

Intervention group (15 participants)—Will be administered one sachet containing 10 g of creatine twice a day.

Control group (15 participants)—Will be administered one sachet containing 10 g of placebo (maltodextrin) twice a day.

All sachets will be the same color and size. All patients will receive assisted supplementation with powdered milk protein serum isolate, if necessary, to achieve a daily intake of 1.5 g/kg of body weight and standard physiotherapy care. Supplementation will be offered during the 7-day hospitalization.

Rehabilitation will start after the first 24 h of the ictus, and the intensity will be proportional to the benefit and tolerance of each individual. Standard physiotherapy will be performed according to the current rehabilitation guidelines for stroke patients and will consist of contracture prevention, limb and trunk strengthening, gait training, and independence [18, 19].

All individuals will be instructed at the time of hospital discharge on healthy eating habits, and adequate fractioning, and provided incentives for eating fruits, vegetables, and whole grains, and maintaining water intake in accordance with the Dietary Guidelines for the Brazilian Population by the Ministry of Health [20].

Participants who are intolerant to the supplements or who withdraw their consent will be excluded from the study. All patients will be followed up daily and encouraged to consume all meals and study products. If necessary, substitutions will be made to the patient’s diet with similar foods to promote supplementation acceptance during the intervention period.

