### Procedures (template)

All patients with ischemic stroke confirmed by imaging examinations who meet the study inclusion criteria will be invited to participate. After signing the informed consent form, the patients will be randomized to the intervention or control groups. All patients will undergo clinical and neurological evaluations conducted by the medical team using the NIHSS score, which is used to determine treatment and predict prognosis; Bamford classification according to brain injury location; and the Alberta Stroke Program Early CT Score (ASPECTS), which verifies the extent of the injury [1, 21].

The template for the recommended schedule of enrollment, interventions, and assessments is presented in Fig. 2. To verify the occurrence of mortality, we will utilize death certificates from medical records.

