### Statistical analysis

The Full Analysis Set (FAS) will comprise all randomized subjects who have received at least one dose of creatine. The subjects will contribute to the analysis as randomized. The FAS will be used for efficacy analysis instead of intention-to-treat analysis.

The Per-Protocol (PP) population will comprise all subjects in the FAS who do not have any major protocol deviations (including but not limited to violation of inclusion and exclusion criteria), and who have at least good compliance as reported in the eCRF and for whom the primary endpoint can be derived. The PP will be used for the analysis of the primary endpoint.

The Safety Analysis Set will comprise all subjects who have received at least one dose of creatine or placebo. The subjects will contribute to the analysis as actually treated. The Safety Analysis Set will be used for the evaluation of safety endpoints and the primary endpoint.

Missing values will be treated mathematically by multiple imputation.

All data will be analyzed using Stata SE version 15.0 (StataCorp LLC., College Station, TX, USA).

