## Discussion

This clinical trial encompasses the use of creatine in the acute phase of stroke. Indeed, research about therapeutic strategies to mitigate the muscle mass decline after stroke is urgent. In general, the researches are focused on assessment, instead of treatment.

The limitation of the study is the sample size. However, the studies involving nutritional interventions to old people are a big deal, because of compliance and preferences. In addition, the stroke may add an extra difficulty because of the chance of conscience level, dysphagia, and tube feeding. In fact, studies published in a systematic review involving creatine supplementation in different scenarios included an average of 10 patients per group, showing that creatine might exert benefits for muscle mass and function [16]. On the other hand, the study will be rigorously conducted inside a stroke unit, with intake control, standardized care, and monitoring.

In addition, the trial may bring information for next larger studies, especially regarding side effects, compliance, and future sample size calculation. ICaRUS Stroke Trial will not be conducted as a feasibility study because we intend to make an entirely statistical analysis and follow-up.

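### Excluding intolerant participants from the study after randomisation conflicts with the as-randomised analysis set and leaves their day-7 and day-90 outcomes undefined

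*Protocol article*

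**What the plan says.** The conduct rule is in the protocol article under Interventions: "Participants who are intolerant to the supplements or who withdraw their consent will be excluded from the study". It does not say whether exclusion means stopping the product, ending the visits or leaving the analysis.

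The sections that bear on it are:

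- **Participants and eligibility criteria.** Screening already rules out patients with "allergies or intolerance to any component of the study products, and patients who decline to participate".
- **Procedures.** "After signing the informed consent form, the patients will be randomized to the intervention or control groups".
- **Statistical analysis, FAS.** "The Full Analysis Set (FAS) will comprise all randomized subjects who have received at least one dose of creatine", and "The subjects will contribute to the analysis as randomized". No exit for later intolerance is given.
- **Statistical analysis, Safety Analysis Set.** "The Safety Analysis Set will comprise all subjects who have received at least one dose of creatine or placebo", and "The subjects will contribute to the analysis as actually treated".
- **Statistical analysis, missing values.** Multiple imputation is named as the method.
- **Outcomes and Follow-up evaluations.** The biomarker comparison covers everyone randomised, and the day-90 assessments are set for each patient.
- **Planned statistical methods and Data monitoring.** All adverse events are summarised. Gastrointestinal events related to supplementation are reviewed individually with the medical team.

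**The concern.** Intolerance that appears during supplementation can be an effect of the assigned product. A rule that turns such an event into exit from the study lets treatment influence who is left to be compared, and randomisation no longer protects the comparison. The efficacy section takes the opposite position: participants count in the arm to which they were assigned, whatever happens later. Someone who follows the Interventions section and someone who follows the Statistical analysis section would handle the same patient differently.

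The trial has 15 patients per arm, so two or three such patients are a visible share of one arm. The Discussion also says that the trial may inform later work, "especially regarding side effects, compliance, and future sample size calculation". Patients who could not tolerate the product bear directly on that purpose.

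This is a written conduct rule, not detail left to an analysis plan. If it stops the day-7 and day-90 assessments, no later analysis plan can recover them.

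**Working it through.** **Step 1. Does the rule act after randomisation?** Known intolerance is a screening exclusion, and randomisation follows consent. Supplementation starts only after that. The Interventions sentence can therefore only add cases of intolerance that emerge on the assigned product, in participants already randomised.

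**Step 2. The two readings beside the other sections.**

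| Reading of exclusion | FAS, as randomised | Biomarkers in all randomised; day 90 in each patient | Safety data |
|---|---|---|---|
| Removed from analysis | Contradicted | Contradicted | Contradicts membership by one dose |
| Assessments stop | Member in name, outcomes missing | Cannot be carried out | Intolerance event kept; later events may be lost |
| Only the product stops | Consistent | Consistent | Consistent |

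Only the third reading fits the rest of the protocol, and it is not what the sentence says. Under the second, the missing values arise for a reason that may be linked to treatment. Imputation in its usual form assumes that those who left resemble similar patients who stayed.

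**Step 3. The plan's own figure.** The sample size is an average of 10 per arm plus 50%: 10 × 1.5 = 15 per group, 30 in total. This reproduces. No effect size, SD, power or intolerance rate is given, so everything below rests on assumptions.

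**Step 4. Shift in the creatine mean if k of 15 are dropped from that arm only (first reading).** Two ways of describing how the dropped patients differ:

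(a) *Fixed gap.* If they would have done d SD worse than the rest, shift = (k/15) × d.

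| k | d = 0.5 | d = 1.0 |
|---|---|---|
| 1 | 0.033 | 0.067 |
| 2 | 0.067 | 0.133 |
| 3 | 0.100 | 0.200 |

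(b) *Ranking.* The k patients lowest on a variable with correlation r to a standard normal outcome are dropped. Shift = r × S/(15 − k), where S is the expected sum of the k most extreme of 15 standard normal values. Those expected values are 1.736, 1.248 and 0.948.

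| k | S | r = 0.5 | r = 1 |
|---|---|---|---|
| 1 | 1.736 | 0.06 | 1.736/14 = 0.12 |
| 2 | 2.984 | 0.11 | 2.984/13 = 0.23 |
| 3 | 3.932 | 0.16 | 3.932/12 = 0.33 |

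A simulation of 40,000 trials with no true effect agrees with table (b). Across both methods the range is 0.03 to 0.33 SD. If equal numbers are dropped from both arms by the same mechanism, the expected difference between arms is about zero.

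**Step 5. Loss of precision.** The difference detectable with 80% power at two-sided 5% (normal approximation) is (1.960 + 0.842) × √(1/n + 1/15). For n = 15 this is 1.02 SD. For n = 14, 13 and 12 it is 1.04, 1.06 and 1.09 SD. Power at 1.02 SD falls from 80% to about 79%, 77% and 75%. This loss is modest; the possible bias matters more.

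**The case against.** The strongest reply is that the Statistical analysis section governs who is analysed, and it has no removal for later intolerance. On that text, dosed patients stay in the sets, and the Interventions sentence may be loose wording for stopping the product. The sentence after it speaks of daily follow-up of all patients. Gastrointestinal events do not lead automatically to exclusion: each is discussed with the medical team, and dietary substitutions are allowed. The article does not say that data collection ends. All of this stands, and it is why the point is a conflict to resolve rather than proof that patients will be dropped.

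A reader might infer more in four ways that the documents do not support:

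- **That tolerability results lose these patients.** The Safety Analysis Set needs only one dose, and all adverse events are summarised, so the intolerance event is captured. What is at risk is events after exclusion.
- **That every analysis set is as randomised.** Only the FAS, and the per-protocol (PP) subset drawn from it, are. The Safety Analysis Set is as treated. Read literally, the FAS also requires a dose of creatine, which is a separate problem.
- **That the type I error is materially inflated.** Two exclusions can raise it to about 10.8%, but only if all are on creatine, intolerance correlates perfectly with outcome, and patients are deleted and compared by t-test. At correlation 0.5 the figure is about 6.2%, and at 0.25 about 5.3%. The plan names multiple imputation, and mixed models for muscle mass, strength and biomarkers.
- **That the bias favours creatine.** This needs intolerant patients to be sicker and mostly on creatine. The documents show neither. Both arms may also receive the same milk protein, and the staff giving supplements and making assessments are blinded.

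Withdrawal of consent, in the same sentence, is a legitimate reason to stop collecting data and is not part of the fault.

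**Conclusion.** The point holds as a contradiction between a stated conduct rule and the stated analysis population, with harm under either of the two readings in which exclusion goes beyond stopping the product. Removal from analysis breaks the randomised comparison. Stopping assessments leaves primary and follow-up outcomes missing for a possibly treatment-related reason.

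The size cannot be fixed from the documents. The 0.03 to 0.33 SD range assumes 1 to 3 exclusions, creatine arm only, complete removal, and a link to outcome running from a gap of 0.5 SD to perfect correlation. The upper end is a worst case. With no link to outcome, or with balanced exclusions, the expected shift is about zero. The conflict does not depend on these numbers.

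**What to change.** Replace the Interventions sentence with wording that separates stopping the supplement from leaving the study, for example:

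*Participants who stop the supplement because of intolerance and who still consent remain in the study. They have the day-7 and day-90 assessments, are analysed in the FAS in the group to which they were randomised, and are counted in the Safety Analysis Set. Only withdrawal of consent ends further data collection; data obtained up to that point are kept.*

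The clinical decision to stop the supplement is unchanged.

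The cost is one amended sentence and the already scheduled assessments for a small number of patients. The estimated effect is slightly diluted relative to an on-treatment effect, and the planned PP analysis addresses that question. Recruitment began in March 2019, so assessments already missed for anyone excluded earlier cannot be recovered. Those participants should be reported by arm with the reason for exclusion.

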### Outcomes

The primary outcomes will be functional capacity, strength, and changes in muscle mass after the intervention. The evaluations will be conducted in the first 24 hours after stroke and on the 7^th^ day of hospitalization. The patients will be assessed for the following:Functional capacity according to the mRs and Timed Up and Go test scores.Muscle strength according to handgrip strength and lower limb strength according to the National Institutes of Health Stroke Scale (NIHSS) score.Muscle mass by muscle ultrasonography, electrical bioimpedance, and muscle degeneration markers by D3-methylhistidine.

A descriptive and comparative evaluation between groups in order to verify the inflammatory and potential serum biomarkers behavior during hospitalization will be performed with all participants randomized.

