### Follow-up evaluations

A follow-up 90 days after stroke will be conducted to verify functional capacity, muscle strength, mortality, and quality of life. The following will be assessed in each patient:Functional capacity according to the mRs and Timed Up and Go test scores.Muscle strength based on handgrip strength and lower limb strength according to NIHSS score and the 30-s chair stand test score.Patient perception of quality of life according to The European Quality of life Scale Five Dimension (EuroQol-5D) score.

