#### Planned statistical methods

Statistical Considerations Baseline is defined as the randomization visit and the end of the trial is defined as the final visit. Categorical data will be summarized by treatment group, using the number and percentages of subjects.For the calculation of percentages, the denominator will be the number of subjects in the analysis set.Continuous data will be presented using the number of subjects, mean, standard deviation, median, lower quartile, upper quartile, minimum, and maximum. Both the absolute values and the change from baseline will be presented. The treatment group and visit will present descriptive statistics for all endpoints (if applicable). All statistical tests will be carried out as two-sided and performed on a 5 % significance level. Estimated treatment differences and 95% CIs will be presented together with the corresponding *p*-value. All safety endpoints will be presented using descriptive statistics and no formal statistical tests will be applied.The evaluation of continuous variables of the characteristics between the groups will be analyzed by the *t*-test or Mann-Whitney.The assessment of variation of serum levels of biomarkers, muscle mass, and strength between groups and time will be done by the mixed regression models.Kaplan-Meier survival curves will be used to show the survival in the groups within 90 days. Considering day zero as the day of randomization and entering into the study, patients related the final date they had each outcome. This is appropriate as it takes into account what happened during the course of the study. *P*-values were obtained through proportional Cox regression models and a value of 5% was considered statistically significant.All adverse events will be summarized. The summaries will include the number of events, the number of subjects, and the proportion of subjects reporting these events and will be tabulated by system organ class.

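### Seven instruments are all primary at an unadjusted two-sided 5%, the Abstract and Outcomes lists differ, and the single primary endpoint used in the analysis sections is never identified

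*Protocol article*

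**What the plan says.** The Outcomes section of the protocol article opens with "The primary outcomes will be functional capacity, strength, and changes in muscle mass after the intervention". It then assigns instruments to each domain, assessed within 24 hours of stroke and on hospital day 7:

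- Function: "Functional capacity according to the mRs and Timed Up and Go test scores".
- Strength: "Muscle strength according to handgrip strength and lower limb strength according to the National Institutes of Health Stroke Scale (NIHSS) score".
- Muscle mass: "Muscle mass by muscle ultrasonography, electrical bioimpedance, and muscle degeneration markers by D3-methylhistidine".

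The Abstract (Methods) gives the instruments for the primary outcomes as mRS, Timed Up and Go, and "handgrip strength, 30-s chair stand test, muscle ultrasonography, electrical bioimpedance, and identification of muscle degradation markers by D3-methylhistidine". NIHSS is not in that list.

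Follow-up evaluations, which covers day 90, has "Muscle strength based on handgrip strength and lower limb strength according to NIHSS score and the 30-s chair stand test score". Muscle strength assessment, which sits under Baseline assessments, also describes the 30-s chair stand as a measure of lower limb strength.

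Planned statistical methods says "All statistical tests will be carried out as two-sided", at a 5% level. It gives no adjustment, hierarchy or rule for success. Statistical analysis says "The PP will be used for the analysis of the primary endpoint", and admits to the per-protocol set only patients in whom that endpoint can be derived. Sensitivity analysis likewise refers to one primary analysis. Trial design declares a superiority aim, and Randomization and blinding says the statistician is not blinded.

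**The concern.** A superiority trial needs one result, or a stated combination of results, that decides its claim. Here seven measures carry the primary label, eight if both lists are honoured. All are tested at the full 5%, and nothing says which one decides or how many must succeed. A single p-value below 0.05 on any of them could be reported as the primary finding.

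The singular wording in the analysis sections does not settle this, because it points to an endpoint that the document never names. The per-protocol set cannot be constructed until that endpoint is known. The statistician will know the allocation, so an endpoint left open could be settled with the results by arm in view.

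**Working it through.** **The two primary lists**

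| Instrument | Abstract, Methods | Outcomes (day 7) | Elsewhere |
|---|---|---|---|
| mRS | yes | yes | also day 90 |
| Timed Up and Go | yes | yes | also day 90 |
| Handgrip | yes | yes | also day 90 |
| NIHSS leg strength | no | yes | also day 90 |
| 30-s chair stand | yes | no | day 90; also described under Baseline assessments |
| Ultrasonography | yes | yes | |
| Bioimpedance | yes | yes | |
| D3-methylhistidine | yes | yes | 10 of 30 patients only |

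Each list has seven entries. They share six, so their union is 6 + 1 + 1 = 8.

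**The plan's own figure.** The plan states no power and no family-wise error rate. Its only design figure is 15 per group, from an average of 10 per arm in earlier studies plus 50%: 10 × 1.5 = 15. This reproduces, but it rests on no endpoint and so does not show which measure was meant to decide.

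**False-positive rate, either direction.** Inputs: k tests, each at two-sided 0.05, no true effect on any of them, and any one significant result counted as success. For independent tests the rate is 1 − 0.95^k.

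- k = 7: 1 − 0.95^7 = 0.302. The upper bound under any dependence is 7 × 0.05 = 0.35.
- k = 8: 1 − 0.95^8 = 0.337.

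The document gives no correlations. Equally correlated normal test statistics were therefore assumed and simulated (400,000 replicates).

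**False-positive rate favouring creatine.** Each test has a 2.5% chance of a false result in that direction. For seven independent tests: 1 − 0.975^7 = 0.162.

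| Assumed correlation, k = 7 | Any false positive | Favouring creatine |
|---|---|---|
| 0 | 30% | 16% |
| 0.3 | 27% | 14% |
| 0.5 | 23% | 12% |
| 0.7 | 18% | 9% |
| 0.9 | 11% | 6% |
| One test, for reference | 5% | 2.5% |

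**If each side and muscle were tested separately (an assumption).** Ultrasound is taken on two muscles and both sides, handgrip on both sides, and the NIHSS leg item on both legs. The count is mRS 1 + Timed Up and Go 1 + handgrip 2 + NIHSS 2 + ultrasound 4 + bioimpedance 1 + D3-methylhistidine 1 = 12. If independent, 1 − 0.95^12 = 0.460 in either direction and 1 − 0.975^12 = 0.262 favouring creatine. At correlations of 0.3, 0.5 and 0.7 the two-sided rate is 40%, 32% and 23%.

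**Cost of controlling the error.** For a continuous measure compared by t-test with 15 per group, the detectable difference d (in SD) solves P(T > t(1 − α/2, 28)) = 0.80. Here T is noncentral t with 28 degrees of freedom and noncentrality d × √(15/2).

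- α = 0.05: d = 1.06.
- α = 0.05/3 = 0.0167 (strictest Holm step, three primaries): d = 1.25.
- α = 0.05/7 = 0.0071 (Bonferroni over all seven): d = 1.38.

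**The case against.** **A separate analysis plan may deal with multiplicity.** That is fair as far as the choice of adjustment method goes, and its absence alone would be no finding. It does not cover what this article states: a 5% level for every test, two primary lists that conflict, and reliance on one endpoint that it does not name. Nor can the trial be excused as exploratory. It declares superiority, and its Discussion says it will not be run as a feasibility study.

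**The rates depend on a success rule that the document does not give.** This stands. If every primary had to be significant, the error would not exceed 5%. The figures show what the text permits, not what the investigators intend.

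**A false claim of efficacy is not likely.** A reader might infer from seven tests at 5% that it is. The numbers do not support that. The chance of a false result favouring creatine is 6-16%; even 12 independent tests give 26%. These are well above nominal but below one half.

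**The 12-test count is inferred.** This also stands. The document describes measurements on both sides but does not say they are tested separately, and the planned mixed models could hold both sides in one analysis.

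**The Abstract may not be the list in error.** A reader might take the chair stand to be a day-90 measure that strayed into the Abstract. Its description under Baseline assessments leaves open that the Outcomes section omitted it, and the schedule figure was not available to this review. That the lists differ is established; which one is wrong is not.

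**Conclusion.** The point holds and should be corrected. The document does not fix which result decides its superiority claim, prints two different primary lists, and defines an analysis set by an endpoint it never identifies.

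The inflation is from 5% to as much as about 30% for seven instruments, and to about 6-16% against 2.5% for a false result favouring creatine. These figures rest on three assumptions: any single significant instrument counts as success, creatine has no effect on any instrument, and the correlations lie in the range shown. The 46% figure needs the further assumption of separate tests by side and muscle, and is an outer case only.

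The contradiction between the lists and the unidentified endpoint depend on none of these assumptions.

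**What to change.** 1. Reconcile the Abstract, Outcomes, Follow-up evaluations and Muscle strength assessment into one primary list, stating when the 30-s chair stand and the NIHSS leg item are measured and what status each has.
2. Before anyone, including the unblinded statistician, sees outcome data by arm, choose one of two routes. Either name a single primary measure, fixing the instrument, the side or muscle where relevant, and day 7; or name one measure per domain on the same terms and test the three with Holm at an overall 5%. The document gives no basis for ranking the instruments, so the choice is the sponsor's.
3. Make all other measures, sides and time points secondary, reported as estimates with 95% confidence intervals.
4. Analyse all randomized patients in both arms. The full analysis set must be reworded first: read literally, it admits only patients who took creatine and so leaves out the placebo arm.
5. State the model for the chosen measure. The planned mixed models cover biomarkers, muscle mass and strength, so a functional measure such as mRS has no clearly assigned analysis.

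This is a change of wording and needs no extra patients or data. With three primaries, the detectable difference for a continuous measure rises from 1.06 to 1.25 SD at the strictest Holm step; that t-test figure does not carry over to the ordinal mRS. Keeping all seven under Bonferroni would raise it to 1.38 SD. A single primary leaves it at 1.06 SD. Recruitment began in March 2019, so the choice should be dated, with a statement of who had seen data by arm at that point.
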